## **4. VARIABLES AND EPIDEMIOLOGICAL MEASUREMENTS**

### **4.1 Exposures**

Not applicable; there are no drug exposures in this study.

### **4.2 Outcomes**

#### **Case Definition – Undiagnosed Stage 3 CKD**

Patients with undiagnosed stage 3A-3B CKD will be identified if they have no healthcare encounter with a diagnosis code for CKD at any time during the  $\geq 12$ -month lookback period before the first eGFR measurement and up to 6 months post-index date (baseline period). Those with a documented diagnosis of CKD during this time period will be considered as having diagnosed CKD. It will be assumed that patients with at least one diagnostic code for CKD during the above specified time window have diagnosed CKD. 错误!未找到引用源。 below shows the study schematic.

**Figure 1. Study suggested schematic(s) below**

[figure not shown]

The total number of the hospitals will be included is 20 (excluding the 4 hospitals with only nephrology data)

CKD, chronic kidney disease; eGFR, estimated glomerular filtration rate

## CKD management and monitoring

To assess the current state of CKD management and monitoring practices by CKD diagnosis status, information on quality indicators will be extracted in the following seven domains starting six-months post index date.

### 1. Detection and recognition of CKD

- Patients receiving a UACR test within first 6 months of follow-up

### 2. Monitoring of kidney function and complications

Patients receiving the following tests within first 18 months of follow-up

- Serum Cr test (outpatient)
- Patients receiving a UACR test (outpatient)
- Serum calcium
- Phosphate
- Albumin
- Bicarbonate
- Potassium
- Hemoglobin
- Albuminuria

### 3. Use of recommended medications

- Statin prescription within one year
- ACEis or ARBs within one year
- SGLT2 in patients with diabetes
- SGLT2 in patients without diabetes

### 4. Kidney function monitoring after initiation of ACEIs or ARBs

- Patients who receive an outpatient serum creatinine measurement 7-30 days after initial ACEi or ARB prescription

### 5. Kidney function monitoring after initiation of SGLT2i

- Patients who receive an outpatient serum creatinine measurement 7-30 days after initial SGLT2i prescription

### 6. Management of BP

- Patients receiving BP measurement any time during follow-up
- At least one BP measurement within 6 months
- In patients with least one BP measurement within 6 months (starting 6 months post index), patients with at least one BP measurement  $\leq 140/90$  mm Hg in the first or second year of follow-up
- In patients with least one BP measurement within 6 months (starting 6 months post index), patients with at least one systolic BP measurement  $< 120$  mm Hg in the first or second year of follow-up

### 7. Monitoring of glycaemic control

- Patients with a history of diabetes prior to the index date receiving an HbA1c test within the first and second year of follow-up

## 4.3 Other Variables and Covariates

The following baseline variables will be examined. Unless otherwise specified, medical history/comorbidity will be assessed using all available data prior to the index date. Baseline physiological and laboratory values will be extracted at the point of index date or using the most recent values during the 12 months before the index date. Similarly, medication use will be ascertained on or within 12 months before the index date.

#### 4.3.1 Baseline Patient Characteristics and Comorbidities

The following baseline characteristics will be assessed:

- *Demographic variables*
  - Age in years at index date, continuous and categorical (<45, 45-<65, 65-<75, ≥75 years)
  - Sex, categorical (female, male, not available)
  - Ethnicity (or education if available) categorical
  - Family history of CKD
  - Smoking status
  
- *Physiological/laboratory values*
  - Height (cm), continuous
  - Weight (kg), continuous
  - Body mass index (BMI), continuous, calculated as  $\text{kg/m}^2$  where  $kg$  is weight and  $m$  is height
  - Hemoglobin (Hb), g/dL
    - Hb >12
    - Hb 10-12
    - Hb 8-10
    - Hb <8
  - Hematocrit
    - <40%
  - eGFR (mL/min/1.73m^2) using CKD-EPI or MDRD equation, continuous
  - Potassium, highest and closest to index date within 1 year prior to index, mmol/l
    - 5.5–5.9 (mild hyperkalemia)
    - 6.0–6.4 (moderate hyperkalemia)
    - >6.5 (severe hyperkalemia)
  - Urine albumin creatinine ratio (UACR, mg/g), continuous, calculated as urine albumin (mg/dL) / urine creatinine (g/dL)
  - Serum uric acid levels, continuous
  - Total cholesterol, continuous
  - Low density lipoprotein (LDL) cholesterol, continuous

- High density lipoprotein (HDL) cholesterol, continuous
- Triglycerides, continuous
- Serum calcium, continuous
- Serum phosphate, continuous
- Serum bicarbonate, continuous
- Albuminuria, continuous
- Serum albumin, continuous
  
- *Medications*
  - Cardiovascular
    - ACE inhibitors
    - ARBs
    - Aldosterone receptor agonists (MRA)
    - Angiotensin receptor-neprilysin inhibitor (ARNI)
    - Loop diuretics
    - Beta blockers
    - Thiazide diuretics
    - Calcium channel blockers
    - Alpha blockers, e.g., clonidine and methyldopa
  - Glucose-lowering drugs
    - Metformin
    - Sulphonylurea
    - Dipeptidyl peptidase 4 inhibitors (DPP-4i)
    - Glucagon-like peptide-1 receptor agonist (GLP1-RA)
    - Insulin
    - Other oral anti-diabetes (OADs), (sulfonylureas, thiazolidinediones, biguanides, alpha-glucosidase inhibitors)
  - Lipid-lowering drugs
  - SGLT2 inhibitors
  - Antithrombotic/antiplatelet agents
  - Anticoagulants
  
- *Medical history/comorbidities*
  - Atherosclerotic cardiovascular disease (ASCVD)
    - Myocardial infarction (MI)
    - Unstable angina (UA)

- Stable angina
  - Coronary revascularization
  - Stroke (ischemic or hemorrhagic)
- Heart failure
- Atrial fibrillation
- Peripheral arterial disease (PAD)
- Diabetes mellitus
  - Type 1 diabetes (T1D)
  - Type 2 diabetes (T2D)
  - Unclassified diabetes
- Hypertension
- Glomerulonephritis
- Hyperkalemia
- Hypertensive kidney failure
- Diabetic nephropathy
- Acute kidney injury (using diagnostics codes)
- Unspecified kidney disease
- Gout
- Poly cystic kidney disease
- Lupus
- Number of clinic visits in the year before the index date

#### **4.4 Study Subgroups**

The following study subgroups will be examined as part of this analysis:

- Age (in years)
- Gender
- Ethnicity
- T2D (Yes vs. No)
- Heart failure (Yes vs. No)
- T2D and heart failure
- Anemia (Yes vs. No)
- Hypertension (Yes vs. No)
- CKD stage 3a vs 3b
- UACR (<30, 30-300, >300 mg/g)

- Health care setting where eGFR is measured (inpatient vs outpatient)
- Etiology of CKD (Glomerulonephritis, Hypertensive kidney failure, Diabetic nephropathy, Acute kidney injury, Unspecified kidney disease)
- Established CVD (history of MI, stroke, CABG, PCI or unstable angina)

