### 3.3 Study Population

Patients  $\geq 18$  years old with two consecutive eGFR measurements indicating stage 3 CKD ( $\geq 30$  and  $< 60$  mL/min/1.73m^2 using CKD-EPI (preferred) or MDRD equation) recorded more than 90 days apart (max. 730 days), meeting the inclusion criteria will be included in the study and constitute the denominator for the calculation of the prevalence of undiagnosed stage 3 CKD. A subset of the study population will be identified with no encounters with a diagnosis code for CKD any time prior to the study index date (for primary objective 2). The observation period will vary based on the period of data coverage, which may be unique to each data source. In CRDS database observation start date will be January 1, 2015, and observation end date will be 31 December 2020.

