#### Inclusion criteria

1. At least two consecutive eGFR laboratory tests with values  $\geq 30$  and  $< 60$  mL/min/1.73 m^2 (Stage 3A or 3B) that are  $> 90$  and  $\leq 730$  days apart. The index date is the date of the second eGFR measure meeting the criteria for stage 3 CKD
2. At least 12 months of continuous presence in the database or registration in the data prior to the first qualifying eGFR (for data sources with information on enrollment)
3. Age  $\geq 18$  years at index date

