#### Exclusion criteria

Patients will be excluded if they meet the following criteria:

1. Solid organ transplant before the study index date
2. Any evidence of advanced CKD (stage 4, 5) based on CKD diagnostic codes, or renal replacement therapy before the index date

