## **5.3 Bias**

### **5.3.1 Methods to Minimize Bias**

The identification of patients with undiagnosed vs. diagnosed CKD relies on laboratory eGFR results, and the assumption that the absence of a CKD diagnosis code (e.g., ICD 9/10)

indicates that the patient is yet to be diagnosed with the condition by the physician. As this information is being inferred from EMR records, our assumptions may result in the misclassification of patients. The accuracy of our algorithm to identify patients with undiagnosed CKD is unknown. However, bias due to misclassification should be minimized, as our definition of CKD using eGFR results is based on an established clinical definition. Additionally, for patients identified as “undiagnosed”, we will also examine whether therapies for CKD (e.g., ACEi, ARB) are administered in the 12 month period following the index date (2nd eGFR result between 30-<60) to understand the likelihood that the patient is actually undiagnosed e.g., a code for CKD does not appear in their medical records but they are receiving treatment for CKD.

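### Inpatient and AKI-period eGFRs can qualify a patient for cohort 1, and no planned analysis removes patients whose two low values were both transient

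*Protocol*

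**What the plan says.** - **Entry (section 3.4, inclusion criterion 1).** The rule is "At least two consecutive eGFR laboratory tests with values" in the stage 3 range; section 3.3 gives the spacing as "recorded more than 90 days apart (max. 730 days". On timing, "The index date is the date of the second eGFR measure meeting the criteria for stage 3 CKD". Neither section sets a condition on care setting or clinical stability.
- **Exclusions (section 3.4).** There are two: "Solid organ transplant before the study index date", and "Any evidence of advanced CKD (stage 4, 5) based on CKD diagnostic codes, or renal replacement therapy before the index date". AKI is in neither.
- **Where setting and AKI do appear.** Section 4.4 has the subgroup "Health care setting where eGFR is measured (inpatient vs outpatient" and lists AKI as one level of CKD etiology. Section 4.3.1 lists "Acute kidney injury (using diagnostics codes" under medical history. Section 5.2 stratifies the primary prevalence by the section 4.4 subgroups.
- **Source (section 3.2).** CRDS draws on Grade 3A hospitals, and 20 remain once nephrology-only sites are dropped.
- **Codes (Table A1).** The primary definition contains no acute renal failure codes. Sensitivity analysis 2 adds them, including N17, as codes that make a patient diagnosed.
- **Stated protection (section 5.3.1).** The protocol argues that "bias due to misclassification should be minimized, as our definition of CKD using eGFR results is based on an established clinical definition". Section 1.1 describes the usual diagnosis as reduced function lasting more than 3 months. The limitations in section 5.3.3 do not mention transient falls.

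**The concern.** The eGFR pair stands in for sustained loss of function. In a hospital database, someone admitted twice with an acute illness, more than 90 days apart, can have a temporarily low eGFR each time and no test recorded in between. That patient meets inclusion criterion 1 without having shown the persistence that section 1.1 describes. A clinician would have no reason to enter a CKD code, and a code for AKI alone does not count as a CKD diagnosis under the primary definition. The patient then falls in the numerator.

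The headline figure will be read as CKD that physicians missed, and for these patients there may have been none to find. Time to diagnosis is exposed in the same way, because the same patients enter cohort 2 and may never receive a CKD code. Sample size does not reduce an error of this kind.

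**Working it through.** **Inputs from the protocol.** Section 5.5 gives an expected prevalence of 60% to 80%, n = 1,000 for a margin of ±3 points, and about 27,000 eligible patients in CRDS. Section 5.2 specifies a binomial 95% CI.

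**Step 1: the plan's own figure.** The half-width is 1.96·√(p(1−p)/n).

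| p | n = 1,000 | n needed for ±3 points | n = 27,000 |
|---|---|---|---|
| 60% | 3.04 | 1,025 | 0.58 |
| 70% | 2.84 | 897 | 0.55 |
| 80% | 2.48 | 683 | 0.48 |

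The stated 1,000 is reproduced: the worst case of 1,025 is within 3% of it. At the cohort size actually expected, random error is only 0.5 to 0.6 points.

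**Step 2: effect of transient pairs.** Let f be the share of cohort 1 that qualified only on transient falls, u the share of those with no CKD code, and p the prevalence among true stage 3 patients.

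Observed = (1−f)·p + f·u, so bias = f·(u−p).

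The documents give neither f nor u. With u assumed to be 95%, the observed prevalence is:

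| p | f = 5% | f = 10% | f = 20% |
|---|---|---|---|
| 60% | 61.75% | 63.5% | 67.0% |
| 70% | 71.25% | 72.5% | 75.0% |
| 80% | 80.75% | 81.5% | 83.0% |

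Example: 0.90 × 60% + 0.10 × 95% = 54.0% + 9.5% = 63.5%, a shift of +3.5 points.

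**Step 3: how large f must be to matter.** Put bias equal to a threshold and solve f = threshold/(u−p), with u = 95% and p = 60%, 70%, 80%.
- For the 3-point planning margin: 3/35 = 8.6%, 3/25 = 12%, 3/15 = 20%.
- For the half-width at 27,000: 0.584/35 = 1.7%, 0.547/25 = 2.2%, 0.477/15 = 3.2%.

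**Step 4: direction.** The bias is upward if u > p, zero if u = p and downward if u < p. With u = 50% and f = 10%, a true 60% would read 59.0%.

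**Step 5: what each planned analysis does with these patients.**
- Sensitivity analysis 1 narrows the code list to stage 3 or higher. They stay in.
- Sensitivity analysis 2 reclassifies those with an AKI code as diagnosed CKD. They leave the numerator but stay in the denominator, and many other renal codes are added at the same time.
- Sensitivity analysis 3 changes inclusion criterion 2 only. They stay in.
- The setting and AKI subgroups report separate prevalences. The overall figure is unchanged, and the protocol does not say which of the two eGFRs fixes the setting.
- The check on ACEi and ARB use after index (section 5.3.1) looks for patients who are treated but not coded. It does not test whether CKD was present.

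**The case against.** The strongest reply is that the protocol is better protected than the bare criteria suggest.

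- **The pair must be consecutive and more than 90 days apart.** Read literally, any recorded value outside the range between the two tests breaks the pair. With serial inpatient testing, the pair would be the last value of one admission and the first of the next, so a patient who recovers before discharge does not qualify. This stands, and it narrows the route. It works only when the recovery is recorded in CRDS. Section 5.3.3 concedes that diagnoses may be made in settings that do not contribute data, and follow-up tests could be missed in the same way.
- **Setting and AKI strata are already planned, and sensitivity analysis 2 takes AKI-coded patients out of the numerator.** This also stands in part, and it would be wrong to say that nothing planned touches AKI. But sensitivity analysis 2 relabels these patients as diagnosed CKD, and its wide code list does not isolate AKI.
- **Section 5.3.1 itself admits possible misclassification and unknown accuracy.** True, but its reassurance rests on the eGFR definition, which is the part at issue here.

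A reader might go further and infer that the headline prevalence is inflated by about the 3-point margin. The documents do not support that: they give neither f nor u, and at p = 80% a 10% share shifts the figure by only 1.5 points. Nor do they show that inclusion criterion 1 must be rewritten or AKI struck from the etiology list. AKI may precede lasting CKD, and no section says otherwise.

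**Conclusion.** The gap is real, and its size is unknown. The protocol lets inpatient and AKI-period eGFRs qualify. A patient with two transient falls and no recorded recovery between them enters cohort 1 and will probably be counted as undiagnosed. No planned analysis removes such patients from both numerator and denominator.

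With u assumed to be 95%, a 10% share would shift true prevalences of 60%, 70% and 80% by +3.5, +2.5 and +1.5 points. A share of about 2% to 3% would already exceed the half-width at about 27,000 patients. The upward direction requires that these patients lack CKD codes more often than true stage 3 patients do; that is likely but assumed.

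This calls for an added analysis and clearer wording. It does not call for a different primary population.

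**What to change.** 1. Leave inclusion criterion 1 as it is. Add to section 5.2 a named sensitivity analysis of the primary prevalence and of time to diagnosis, restricted to patients whose two qualifying eGFRs were both outpatient and neither of which was taken during, or within 90 days after, an AKI-coded encounter.
2. In section 4.4, define the setting subgroup on both values: both outpatient, mixed, both inpatient.
3. In sections 5.3.1 and 5.3.3, name transient falls in eGFR as a source of misclassification.

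**Cost.** The restricted analysis will be smaller. The starting point is about 27,000 against a stated need of 1,000, but the documents do not say how many pairs in this hospital source are both outpatient. Section 4.3 specifies AKI only as history before index, so eGFR dates must be linked to dated AKI encounters. Some patients with true CKD who also had AKI will be dropped. AKI that was never coded is caught only by the outpatient restriction.

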## **5. STATISTICAL ANALYSIS PLAN**

### **5.1 Statistical Methods – General Aspects**

This study is purely descriptive without any formal hypotheses. The main focus will be on quantifying the prevalence and consequences of undiagnosed CKD. Key assumptions include: our ability to define undiagnosed CKD subjects with only eGFR as an indicator of a future diagnosis of CKD by a physician, secondly, that absence of claims or health record data for CKD or other comorbid events indicate that the diagnosis of the condition never occurred, and finally, the timing of recorded CKD diagnosis in the database corresponds with the time when the first CKD diagnosis was made by the health care provider (assuming minimum lag in data recording).

Missing data for baseline measures will be assessed and addressed as a categorical variable with a level for missingness. All reported measures will be summarized in the study tables. Point estimates and their 95% C.I.s will be presented in the final analyses.

Data analysis will take place in a step-wise approach where the objectives pertinent to the describing the undiagnosed CKD patient cohort will be performed first and results will be reviewed by the study team before the analysis on the rest of the objectives take place.

### **5.2 Statistical Analyses**

#### **Baseline characteristics**

Baseline characteristics will be described for the study population. Categorical variables will be summarized using patient counts with percentages, and continuous variables will be summarized using means with standard deviations (SDs), medians with interquartile ranges (IQRs), and minimum and maximum values.

#### **Primary objective**

- *Estimation of the prevalence of undiagnosed stage 3 CKD*

The prevalence numerator will include all patients who fulfill the undiagnosed stage 3 CKD case definition (see [section 4.2](#)) at any time during the observation period. The prevalence denominator will include all individuals meeting the inclusion criteria for this study (cohort 1). Prevalence will be estimated by dividing the numerator by the denominator, and 95% CIs around prevalence will be estimated using a binomial distribution. The denominator population should be the source of cases for the numerator. The prevalence of undiagnosed

stage 3 CKD (cohort 2) will be stratified according to patient subgroups of interest ([section 4.4](#)).

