### CKD management and monitoring

To assess the current state of CKD management and monitoring practices by CKD diagnosis status, information on quality indicators will be extracted in the following seven domains starting 6 months post index date:

1. Detection and recognition of CKD (e.g. UACR testing within 6 months)
2. Monitoring of kidney function and complications (e.g. serum creatinine measurement within 18 months)
3. Use of recommended medications (e.g. ACEIs, ARBs or SGLT2i)
4. Kidney function monitoring after initiation of ACEIs ARBs
5. Kidney function monitoring after initiation of SGLT2i
6. Management of blood pressure
7. Monitoring of glycaemic control

**Statistical Analysis:** The prevalence of undiagnosed stage 3 CKD will be calculated. The prevalence numerator will include all patients who fulfill the undiagnosed stage 3 CKD case

definition at any time during the observation period. The denominator will include all individuals included in the study (cohort 1).

Prevalence will be estimated by dividing the numerator by the denominator, and 95% confidence intervals (CI) around prevalence will be estimated using a binomial distribution. Prevalence will be assessed during the observation period and by each calendar year of the index date. Prevalence will also be calculated among subgroups of patients based on age, sex, and the presence of key baseline comorbidities. For those with no CKD diagnosis code on or before the index date (cohort 2), time to CKD diagnosis will be assessed using KM curve.

Baseline characteristic (at index date) will be described for undiagnosed versus diagnosed CKD. The proportion of patients achieving each of the specified quality indicators will be described by CKD diagnosis status, overall and by comorbidities.

**Sample Size Estimation:** If the prevalence rate of undiagnosed CKD is between 60% and 80%, then a sample of 1,000 patients will be sufficient to estimate the prevalence rate with a margin of error of  $\pm 3\%$  in a 95% CI per institution/country (6% width of 95% CI).

According to the feasibility assessment of REVEAL-CKD in China, the number of patients who meet the inclusion and exclusion criteria in the Chinese Renal Disease Data System (CRDS) database is about 27,000 and the number of patients who met the inclusion and exclusion criteria of sensitivity analysis in the CRDS database is about 46,000^3.

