### Sensitivity Analysis

To calculate the robustness of our undiagnosed CKD definition (identified through 2 eGFR measures and no ICD-9/10 CKD diagnosis codes, and OHDSI ICD-10 CN2016 is used in the CRDS database), we will conduct sensitivity analyses 1-2 that assess whether the lack of healthcare encounters, as originally defined, truly captures an undiagnosed population.

Sensitivity analysis for undiagnosed CKD includes ICD-9/10 diagnosis codes for stage 3 CKD or higher

Sensitivity analysis for undiagnosed CKD includes ICD-9/10 diagnosis codes for CKD based on a broader definition derived by Winkelmayr *et al.*, 2005 ([section 8](#)). We will conduct sensitivity analysis 3 to assess if we have included sufficient individuals with undiagnosed CKD in the database, as required by study inclusion [criteria 2](#).

Sensitivity analysis for adjustment of inclusion criteria 2 from “at least 12 months of continuous presence in the database or registration in the data prior to the first qualifying eGFR (for data sources with information on enrollment)” to “at least one medical visit with diagnostic record within  $\leq 12$  months prior to the first qualifying eGFR”. There are no changes in any other inclusion and exclusion criteria. Analyze undiagnosed CKD according to the primary study definitions using eGFR measures captured within a specific time period prior to diagnosis.

- *Time to CKD diagnosis*

For the cohort of patients with no CKD diagnosis code as of the study index date (cohort 2), the median (95% CI) time in days/months from the study index date to physician-diagnosed CKD (using the primary CKD study definition) will be calculated using the Kaplan-Meier method. Survival times will be censored as of the last day of follow-up for patients who remain undiagnosed by a physician. Time to physician diagnosis of CKD will be calculated overall and by patient characteristics and comorbidities. If possible, association between baseline characteristics and time to CKD diagnosis will be assessed using relevant regression models. The time to physician diagnosed stage 3 CKD or higher (sensitivity analysis #1) and the time to CKD using a broader definition (sensitivity analysis #2) ([section 8](#)) will also be calculated.

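### Section 5.2 labels the subgroup prevalence of undiagnosed stage 3 CKD as cohort 2, which is neither the prevalence denominator nor the undiagnosed group; read literally, the label gives subgroup figures at or above the correct value

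*Protocol*

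**What the plan says.** The paragraph on the primary objective in section 5.2 first fixes the overall estimate: the numerator is the patients who meet the section 4.2 case definition, and "The prevalence denominator will include all individuals meeting the inclusion criteria for this study (cohort 1". The Synopsis (Statistical Analysis) agrees: "The denominator will include all individuals included in the study (cohort 1". Table 1 likewise divides by all patients with an eGFR in the stage 3 range.

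The last sentence of the same paragraph in section 5.2 then says that the prevalence of undiagnosed "stage 3 CKD (cohort 2) will be stratified according to patient subgroups of interest", pointing to section 4.4 for the subgroups.

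Cohort 2 is a defined term. The Synopsis has "For those with no CKD diagnosis code on or before the index date (cohort 2), time to CKD diagnosis will be assessed using KM curve". Section 5.2, on time to diagnosis, has "For the cohort of patients with no CKD diagnosis code as of the study index date (cohort 2". Section 3.3 and the Synopsis (Study Population) describe a subset without an earlier CKD code and assign it to primary objective 2.

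The undiagnosed group is defined in section 4.2 over a longer window, the "lookback period before the first eGFR measurement and up to 6 months post-index date (baseline period".

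**The concern.** A cohort label in an analysis rule tells the programmer which records to select. Here the label names the population of primary objective 2 inside an estimate for primary objective 1. There are two literal ways to use it, and neither matches the rest of the protocol.

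- **Cohort 2 as denominator.** This removes everyone coded by index. It conflicts with the Synopsis, Table 1 and the earlier sentence of section 5.2.
- **Cohort 2 as the undiagnosed group (numerator).** This counts patients first coded in the 6 months after index as undiagnosed. It conflicts with section 4.2, and with the rule under Trends over time in section 5.2, which classes such patients as diagnosed.

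Section 4.4 lists many subgroups, and the overall aim in section 2 includes predictors of undiagnosed disease. Subgroup figures on a different base could not be set beside the overall prevalence, and differences between subgroups in coding before index could be hidden. Section 6.1.2 gives the programming to a local vendor, so the written rule matters.

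**Working it through.** **Plan's own figure.** Section 5.5 states that 1,000 patients give a margin of ±3 points for a prevalence of 60% to 80%. With half-width = 1.96 × √(p(1−p)/n), n = 1,000 gives 3.04 points at p = 0.60, 2.84 at 0.70 and 2.48 at 0.80. The figure is reproduced, apart from rounding at 60% (exactly 3 points would need 1,025). It is not affected by this point and serves only as a yardstick.

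**Notation.** C1 = cohort 1; C2 = cohort 2; U = undiagnosed cases by section 4.2. Let p = U/C1 be the correct prevalence, and r the share of C1 first coded between index and 6 months after.

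**Structure.** Assume that codes before index are searched over the same data for both definitions. Every undiagnosed case is then uncoded at index, so U lies within C2, and C2 lies within C1. C2 consists of U plus those first coded in months 0 to 6, so C2/C1 = p + r.

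- C2 as denominator: U/C2 = p/(p + r). This is at least p, with equality only if nobody is coded by index.
- C2 as numerator: C2/C1 = p + r. This is at least p, with equality only if r = 0.

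**Illustration.** The range of p comes from section 5.5. The protocol does not give r; 2% to 10% is an assumption.

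| p | r | Coded by index (1 − p − r) | U/C2 | C2/C1 |
|---|---|---|---|---|
| 60% | 2% | 38% | 0.60/0.62 = 96.8% | 62% |
| 60% | 10% | 30% | 0.60/0.70 = 85.7% | 70% |
| 70% | 2% | 28% | 0.70/0.72 = 97.2% | 72% |
| 70% | 10% | 20% | 0.70/0.80 = 87.5% | 80% |
| 80% | 2% | 18% | 0.80/0.82 = 97.6% | 82% |
| 80% | 10% | 10% | 0.80/0.90 = 88.9% | 90% |

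Over this grid the denominator use overstates by 8.9 points (88.9 − 80) to 36.8 points (96.8 − 60). The numerator use overstates by r, that is 2 to 10 points.

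**Effect on contrasts (assumed example).** Two subgroups have r = 5%, with 10% and 40% coded by index. The correct prevalences are 85% and 55%, a difference of 30 points. With C2 as denominator they become 0.85/0.90 = 94.4% and 0.55/0.60 = 91.7%, a difference of 2.8 points. With C2 as numerator they become 90% and 60%: the levels rise but the difference stays, because r is equal in the two subgroups.

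**Comparability.** With cohort 1 as the base, subgroup prevalences weighted by size average to the overall p. With C2 as denominator they average, weighted by C2 size, to p/(p + r).

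**The case against.** The strongest reply is that the label is merely loose. It follows the words for undiagnosed disease and does not say that cohort 2 is a denominator. The same paragraph has already fixed both numerator and denominator. The Synopsis introduces the subgroups straight after the cohort 1 denominator without naming another cohort: "Prevalence will also be calculated among subgroups of patients based on age, sex, and the presence of key baseline comorbidities". On that reading numerator and denominator are unchanged and no figure is inflated. This is plausible and limits what can be claimed. It does not rescue the label, because cohort 2 is fixed at index and the undiagnosed group at index plus 6 months.

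Section 5.2 also asks that the denominator be the source of the numerator's cases. That does not settle the matter, since every undiagnosed case also lies in cohort 2 and a cohort 2 denominator would pass the test.

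A reader might infer more than the protocol supports:

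- That the subgroup results will be inflated. This follows only if cohort 2 is actually used.
- That both literal uses contradict section 4.2. That section sets the case definition and no denominator, so only the numerator use contradicts it.
- That subgroup prevalence is part of the stated primary objective 1. The objective names no subgroups; they enter through the Synopsis analysis text and sections 4.4 and 5.2.
- That the error has a known size. The protocol gives neither the share coded by index nor the share coded in the following 6 months.

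**Conclusion.** The label is wrong on every reading, and nothing else in the protocol corrects it. If it is followed literally, the direction is certain given the nesting above: subgroup prevalence is too high or, at best, equal to the correct value, and it is not on the same base as the overall figure. The size cannot be computed from the protocol. Under the assumed r of 2% to 10% and the protocol's 60% to 80%, the denominator use gives about 86% to 98%, in every case well beyond the ±3-point precision target. The numerator use overstates by 2 to 10 points, which at the low end is within that target. If cohort 1 is still intended, the consequence is a mislabelled sentence and no bias. The overall prevalence, the time-to-diagnosis analysis and the sample size are unaffected. The correction should be made because the sentence governs estimates reported under a primary objective.

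**What to change.** In the last sentence of the section 5.2 paragraph on prevalence, replace cohort 2 by cohort 1. Add that each subgroup prevalence is the number of cohort 1 patients in the subgroup who meet the section 4.2 undiagnosed definition, divided by all cohort 1 patients in that subgroup. Keep the term cohort 2 for the time-to-diagnosis analysis only.

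The cost is one sentence in the protocol. Section 6.1 says that a SAP will be created; it was not available for this review, so check whether it or its table shells repeat the label and align them if so. No new data or analyses are needed, and there is no evident downside.
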